### Intervention

Two intervention arms will be assessed: (1) a $AUD20 incremental personal financial incentive; and (2) a $AUD40 incremental personal financial incentive. Women from both intervention groups will have an opportunity to receive a PFI at eight study intervention sessions contingent upon smoking abstinence. The amount of the monetary reward will begin at the base amount (either $AUD20 of $AUD40) and will increase by the base amount (either $AUD20 of $AUD40) at each follow-up that participants are found to abstain from smoking. Smoking abstinence will be assessed through self-report and confirmed by saliva cotinine analysis. Participants in the $AUD20 intervention group, who quit smoking and maintain cessation for the entire eight intervention sessions, will be potentially eligible to receive a total of $AUD720. Participants in the $AUD40 group will be potentially eligible to receive a total of $AUD1440 if they maintain smoking abstinence for the 8 intervention sessions. If a participant fails to abstain at one intervention session or does not present for a scheduled visit they will not receive the incentive for that period. However, the reward amount these women will be eligible for during their next intervention session will be the amount they missed during their previous session. Their potential reward amount will remain at this amount until they have successfully stopped smoking.

### Procedures

All women who visit the hospital antennal clinic will undergo their usual antenatal interview by the clinic nurse. During this interview patients are asked about their smoking status and basic demographic characteristics. At this time potentially eligible patients will be identified and informed that the study is being conducted within the clinic. If women are interested they will be directed to a Research Assistant (RA) who will be stationed within the clinic. The RA will provide interested women with information describing the study. If patients would like to take part in the study the RA will obtain their written informed consent. Women will then be asked to provide a saliva sample to confirm their smoking status and complete a 15-minute baseline Touchscreen computer survey, which will also ask for their on-screen consent.

If a woman’s initial antenatal appointment has been randomised to one of the two intervention groups, the RA will verbally explain the details of their incentive scheme, including, the schedule for monitoring, contingencies being offered and the rules of payment. All participants will be provided with a study package to take home with them, which will contain information about the study, referrals to Quit smoking self-help documents and a Quit telephone help number (provided by clinic midwives) and a letter of support to pass onto their partner. Consenting women will be asked to attend 8 intervention sessions, at which participants in the two intervention groups will be eligible to receive a reward. The 8 intervention sessions will occur approximately fortnightly, during participants’ scheduled antenatal appointments.

During each of the 8 intervention sessions, all women will be asked to indicate their current smoking status and whether they have quit smoking in the last 7 days. Women will also be asked to provide a saliva sample which will be analysed to confirm their self-report smoking abstinence. Those women in the intervention groups who self-report non-smoking and return a negative cotinine reading (level 0) will be provided with their monetary incentive. A similar follow-up procedure will occur seven more times (i.e. a total of 8 intervention sessions) during women’s scheduled antenatal appointment.

During their eighth or final intervention session (i.e. the last follow-up where women are eligible for a reward) women will be asked to provide a hair sample to allow for cotinine analysis using gas chromatography – mass spectrometry. The hair analysis will allow for long-term assessment of women’s smoking status. Women will also be asked to consent to a post-intervention study approximately six weeks after delivery. Women who consent will be contacted via telephone. A short semi-structured telephone interview will be conducted assessing women’s acceptability of the intervention and their current smoking status. A similar interview will be conducted with clinic staff to assess their acceptability of, and feedback on, the program. Both participants and staff will be asked to provide feedback on whether they believe the intervention was useful in increasing smoking abstinence in pregnant women, whether the monetary reward was sufficient and/or delivered in an appropriate manner, whether they believe this intervention could be easily introduced into standard care and whether they experienced any problems with the intervention.

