### Difficulties in accurately verifying women’ smoking status

Due to social stigma and social desirability, women often underreport their current smoking behaviour, making it difficult for clinic staff to accurately verify women’s smoking status
[1]. For example a recent study indicated underestimations of self-reported smoking status during pregnancy by as much as 25%
[10]. The incorporation of simple, rapid, biochemical validation methods of patients’ smoking status, may help to overcome this problem. For instance, a study of family practice patients illustrated validity in using a semi-quantitative dipstick assay (NicAlert®) to rapidly asses participant smoking status through saliva cotinine analysis
[11]. This study illustrated high sensitivity (99%) and high specificity (96%) of the simple, 20-minute analysis of saliva cotinine
[11].

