### Primary outcome measures

The RA will maintain detailed records documenting: (1) the number of eligible women asked to take part in the research study and how many of these women consent to take part; (2) the number of participants who withdraw from the study before study completion; and (3) the number of women who complete or refuse to provide a saliva and/or hair sample for cotinine analysis. This data will be used to measure the following three primary outcomes: (i) consent rates; (ii) loss to follow-up rates of study participants and (iii) participant compliance with saliva and hair cotinine analyses for biochemical validation of smoking status

Semi-structured interviews will be conducted with both participants and clinic staff. Women will be asked a serious of previously published and study specific questions about their experiences and perceptions of the intervention trial. Specifically, six questions previously published by Bryant et al.
[22] will be included in the interviews with study participants, to assess their acceptability of using a touchscreen computer for self-reported smoking status and demographics. Five (5) items previously adapted by the researchers to assess pregnant women’s acceptability of PFI as a strategy to decrease smoking in pregnant women
[21], will be included in both participant and staff interviews. These questions will be used to investigate the acceptability of incentives of varying magnitude to staff and study participants. Open-ended questions will also be included in both participant and staff interviews to assess their thoughts on the acceptability of using saliva and hair cotinine analysis for biochemical validation of smoking status, as well as any perceived barriers and facilitators to using financial invectives.

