### Secondary outcomes

#### Quit rates

Although not adequately powered for detecting small differences in the secondary outcomes, Fisher’s exact test will be used to detect potential differences in smoking cessation rates between groups and to demonstrate potential effectiveness of the intervention. Differences between experimental groups in the secondary outcome - PHQ2 will be assessed using the Kruskal-Wallis test. Fisher’s exact tests will be used to compare conditions on post-partum smoking rates at 6 weeks after delivery.

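### As written, the six-week call is the only described participant source for acceptability and postpartum smoking, and women who stop attending have no described route into it

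*Protocol article*

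**What the plan says.** In the protocol article, Procedures, the relevant paragraph opens: "During their eighth or final intervention session (i.e. the last follow-up where women are eligible for a reward) women will be asked to provide". What is requested at that point is hair for laboratory testing. The paragraph then continues: "Women will also be asked to consent to a post-intervention study approximately six weeks after delivery. Women who consent will be contacted via telephone". On the content of the call it says: "A short semi-structured telephone interview will be conducted assessing". The matters assessed are how acceptable the woman found the intervention and whether she currently smokes.

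Primary outcome measures relies on interviews for participants' views: "Semi-structured interviews will be conducted with both participants and clinic staff". Of the six touchscreen items it says: "will be included in the interviews with study participants, to assess their acceptability of using a touchscreen computer for self-reported smoking status and demographics". Of the five incentive items it says: "will be included in both participant and staff interviews. These questions will be used to investigate the acceptability of incentives of varying magnitude". Staff and women are both meant. Views on saliva and hair testing come from open-ended questions in the same interviews. The only participant interview described, in Study design and in Procedures, is the telephone call after the intervention.

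The Primary outcomes part of the analysis numbers touchscreen acceptability (iv), incentive acceptability (v) and cotinine-testing acceptability (vi). It compares (iv) and (v) between arms by Fisher's exact test and analyses (vi) thematically. Under Secondary outcomes, Quit rates, the use of Fisher's method is stated as: "exact tests will be used to compare conditions on post-partum smoking rates at 6 weeks after delivery".

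**The concern.** The trial's main purpose is feasibility, and acceptability to participants is a large part of it. Women who disliked the scheme, the testing or the survey, or who kept smoking, are plausibly the likeliest to stop attending. If only women present at their last session are invited to the call, the views most informative about unacceptability are not collected. No later analysis can recover them.

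The between-arm comparisons have a further problem. Being asked depends on attendance after randomisation, and attendance may depend on the arm. Under Intervention, incentive-arm women forfeit the reward for a session they miss, while control women have no reward to lose. Economic outcomes measures expects that the intervention may lead women to attend more often than controls do. Comparisons of acceptability and of six-week smoking could then partly reflect who remained to be asked.

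**Working it through.** **Inputs.** From Sample size: 90 women, 30 per arm, 20% drop-out, 60% consent to the trial, 10% ineligible, 208 approached. The article gives no rate of agreement to the call, so I write it as c and take 0.6 to 1.0 as an assumed range.

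**The plan's own figure.** 90 / (0.80 × 0.60 × 0.90) = 208.3, which matches the stated 208. That arithmetic treats 90 as the number left after drop-out (90 / 0.80 = 112.5, so 113 enrolled). Participants and Sample size describe 90 as the number recruited and randomised. I use 90 randomised below. On the other reading, about 113 − 90 = 23 enrolled women would have no interview data, instead of 18.

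**Who can be asked.** 90 × 0.80 = 72, or 24 per arm. At least 18 women (6 per arm, if drop-out is even) give no acceptability or six-week data before anyone declines the call.

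**Who is interviewed, and what that leaves open.** The response fraction is r = 0.80 × c. If a is the acceptability among respondents, the value among all randomised lies between a × r (every non-respondent finds it unacceptable) and a × r + (1 − r) (every non-respondent finds it acceptable). With a = 80% as an illustration:

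| c (assumed) | r | Interviewed (of 90) | Per arm | Range among all randomised |
|---|---|---|---|---|
| 1.0 | 0.80 | 72 | 24.0 | 64% to 84% |
| 0.8 | 0.64 | 58 | 19.2 | 51% to 87% |
| 0.6 | 0.48 | 43 | 14.4 | 38% to 90% |

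For c = 0.8 the line is 0.80 × 0.64 = 0.512 and 0.512 + 0.36 = 0.872.

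**Direction and size of bias.** If all 80% who stay respond, the overstatement is 0.20 × d, where d is the gap in acceptability between stayers and leavers. The article gives no information on d. A gap of 10 points gives 2 points of bias, and a gap of 50 points gives 10. If leavers are no less favourable than stayers, there is no overstatement.

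**Can the last session be recognised?** Eight fortnightly sessions run to about 16 weeks after baseline. Enrolment is open to just under 31 weeks' gestation, so for the latest entrants the eighth session would fall at about 31 + 16 = 47 weeks, after delivery. For these women, and for anyone who simply stops coming, the final session may not be known as final when it takes place. The wording that allows a final session before the eighth does not by itself ensure that the invitation is made.

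**The case against.** The timing of the request is inferred. The sentence on the call gives no time of its own. It follows the hair-sample text and is linked by the word also. Study design refers to a telephone interview of participating women without limiting it to those at the last session. The article is condensed and the consent pages are not shown. This stands as a caution: the article is silent on leavers and does not state that they are barred. The placement is still the natural reading, and if it is wrong a clarifying sentence is needed.

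A reader might infer that drop-outs are missing from the primary outcomes altogether, or that six-week smoking is a primary outcome. The documents support neither. Withdrawals count in loss to follow-up and sample refusals count in compliance, both primary. Six-week smoking is listed under Secondary outcomes, and smoking in pregnancy is recorded separately at baseline and up to eight sessions. Staff acceptability is unaffected.

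A reader might also attach a specific bias to the acceptability figure, or apply the 25% under-reporting cited in the Background to the six-week result. The first would rest on invented rates for leavers. The second figure concerns smoking status during pregnancy, and the protocol does not claim that the six-week status is biochemically verified.

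Finally, this is a proof-of-concept pilot that emphasises confidence intervals, and its loss-to-follow-up outcome will show how many women left. That makes the problem visible but does not supply the missing views. Rules for women not reached can properly sit in an analysis plan, and their absence here is not a fault.

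**Conclusion.** The point holds for the acceptability outcomes obtained from participants (primary iv to vi) and for the secondary six-week smoking comparison. As the Procedures section reads, both depend on being present at the eighth or final session and then agreeing to a call.

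Acceptability may be overstated, and the arm comparisons use a group selected after randomisation. The size cannot be fixed from the documents. With 20% drop-out applied to 90 women, no more than 72 can be asked. With an assumed 60% to 100% agreeing, about 43 to 72 are interviewed. The 51% to 87% range at 80% agreement is a worst-to-best-case bound under an illustrative 80% observed acceptability; it does not forecast the bias. The conclusion rests on the natural reading of when consent for the call is sought and on no other route for leavers being described. It is a moderate design weakness that should be put right because the remedy is cheap.

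**What to change.** 1. Seek consent for the six-week call in the written consent at enrolment.
2. Telephone all randomised women, including those who stopped attending, except any who have refused further contact.
3. Report acceptability among respondents, with the number responding out of all randomised, by arm. Do not use all randomised women as the denominator for acceptability. That would score non-response as rejection and would simply reproduce the lower bound (51% in the middle row of the table).
4. Describe six-week smoking as a secondary, self-reported outcome. Any rule for women not reached can be left to the analysis plan.

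The cost is a consent-form amendment and roughly 20 to 30 extra short calls. The 18 women lost to the planned drop-out set the lower end; at 80% agreement the number not otherwise interviewed is 90 − 58 = 32.

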### Primary outcome measures

The RA will maintain detailed records documenting: (1) the number of eligible women asked to take part in the research study and how many of these women consent to take part; (2) the number of participants who withdraw from the study before study completion; and (3) the number of women who complete or refuse to provide a saliva and/or hair sample for cotinine analysis. This data will be used to measure the following three primary outcomes: (i) consent rates; (ii) loss to follow-up rates of study participants and (iii) participant compliance with saliva and hair cotinine analyses for biochemical validation of smoking status

Semi-structured interviews will be conducted with both participants and clinic staff. Women will be asked a serious of previously published and study specific questions about their experiences and perceptions of the intervention trial. Specifically, six questions previously published by Bryant et al.
[22] will be included in the interviews with study participants, to assess their acceptability of using a touchscreen computer for self-reported smoking status and demographics. Five (5) items previously adapted by the researchers to assess pregnant women’s acceptability of PFI as a strategy to decrease smoking in pregnant women
[21], will be included in both participant and staff interviews. These questions will be used to investigate the acceptability of incentives of varying magnitude to staff and study participants. Open-ended questions will also be included in both participant and staff interviews to assess their thoughts on the acceptability of using saliva and hair cotinine analysis for biochemical validation of smoking status, as well as any perceived barriers and facilitators to using financial invectives.

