### Participants

A sample of ninety (90) consenting pregnant women will be recruited to participate. Women will be considered eligible if they are: (1) aged at least 16 years; (2) presenting for their first antenatal visit; (3) less than 31 weeks gestation; (4) sufficient in English language to complete the survey; and (5) a current smoker (defined as having smoked in last 7 days and a return a positive saliva sample for cotinine). Pregnant women will be ineligible to participate if they have elected to receive shared antenatal care with their GP and/or are considered by clinic staff to have a severe cognitive or psychiatric disorder; currently being treated for chemical dependency other than alcohol or tobacco; or have quit smoking before their first antenatal appointment.

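### The records that define the first three primary outcomes miss silent drop-outs and probably miss women who decline at the nurse interview, so loss to follow-up is biased low, consent is probably too high, and sample compliance depends on how absent women are treated

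*Protocol article*

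**What the plan says.** Under Primary outcome measures, the research assistant keeps three records:

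- consent: "the number of eligible women asked to take part in the research study and how many of these women consent to take part";
- retention: "the number of participants who withdraw from the study before study completion";
- samples: "the number of women who complete or refuse to provide a saliva and/or hair sample for cotinine analysis".

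The section then ties these records to the outcomes: "This data will be used to measure the following three primary outcomes: (i) consent rates; (ii) loss to follow-up rates of study participants", with sample compliance as the third.

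The Procedures section gives the order of contact. The clinic nurse comes first: "At this time potentially eligible patients will be identified and informed that the study is being conducted within the clinic". The assistant comes second: "If women are interested they will be directed to a Research Assistant (RA) who will be stationed within the clinic". After written consent, "Women will then be asked to provide a saliva sample to confirm their smoking status". Yet the Participants section already makes that test part of eligibility, a current smoker being "defined as having smoked in last 7 days and a return a positive saliva sample for cotinine".

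Two other places bear on the point. The Intervention section treats a missed visit as an event with its own payment rule, separate from withdrawal. The Procedures section places the hair sample only at the eighth or final intervention session.

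**The concern.** Feasibility is the primary aim, and these are the first three outcomes that serve it. The article does more than leave their definitions open: it names the data that will measure them, and those data do not fit the procedures described.

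- **Loss to follow-up.** A woman who stops coming but never says that she withdraws is not in the stated count.
- **Consent.** A woman who shows no interest to the nurse never meets the person who keeps the log. In addition, whether a decliner was fully eligible cannot be known, because the saliva test comes after consent.
- **Compliance.** A woman who is absent neither gives nor refuses a sample, so she falls in neither recorded category.

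A main trial would take its recruitment and retention assumptions from these rates. The Analysis section also compares them between arms by Fisher's exact test, so an uncounted first step affects that comparison too.

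**Working it through.** **The plan's own figure.** The Sample size section gives 90 women, 20% drop-out, 60% consent, 10% ineligible and 208 to be approached. 90 / (0.80 × 0.60 × 0.90) = 208.3, so 208 reproduces. Forwards: 208 × 0.90 = 187 eligible, × 0.60 = 112 consenting, × 0.80 = 90 retained. This supplies the planning values used below. It does not say whether the 60% applies to all women told of the study or only to those the assistant sees.

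The documents do not give the share of losses that are formal withdrawals, the share of decliners who stop at the nurse, or the attendance rate. Each is therefore assumed over a range.

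**Loss to follow-up.** Recorded loss = true loss × share that formally withdraws. With a true loss of 20%:

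| Share formally withdrawing | Recorded loss |
|---|---|
| 75% | 0.20 × 0.75 = 15% |
| 50% | 0.20 × 0.50 = 10% |
| 25% | 0.20 × 0.25 = 5% |

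The size depends on the assumed share. The direction does not: the count can only miss losses.

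**Consent, nurse step.** Let s be the share of decliners who stop at the nurse. Recorded consent = 0.60 / (1 − 0.40 × s).

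- s = 25%: 0.60 / 0.90 = 67%.
- s = 50%: 0.60 / 0.80 = 75%.

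The same point from the planning side: suppose the 60% holds only among women who reach the assistant, and a share q of informed women do so. The number to inform is then 208.3 / q, which is 231 (q = 0.90), 278 (q = 0.75) or 417 (q = 0.50).

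**Consent, saliva step.** If a share f of consenters test negative and are removed, while untested decliners stay in the denominator, recorded consent = 0.60 × (1 − f) / (1 − 0.60 × f).

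- f = 5%: 0.570 / 0.970 = 58.8%.
- f = 10%: 0.540 / 0.940 = 57.4%.

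This effect is downward and small beside the nurse-step effect.

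**Compliance.** Among attenders it is 1 − refusal; over all due samples it is attendance × (1 − refusal). With 10% refusal among attenders, the first is 90%. The second is 0.90 × 0.90 = 81%, 0.80 × 0.90 = 72% or 0.70 × 0.90 = 63% at 90%, 80% or 70% attendance. For hair, with 20% absent at the final session and no refusals, the two rates are 100% and 80%.

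**The case against.** The strongest reply is that this is a condensed article and that log mechanics and denominators belong in the full protocol. That covers detail left unsaid. It does not cover a stated data source that conflicts with stated procedures, as with measuring loss by withdrawals.

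Several counter-arguments do stand, and they limit the point:

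- **Consent is not certainly overstated.** A reader might infer that it must be. The article does not say who does the asking, and the 208 women to be approached could be the wider group. If women informed by the nurse are logged, that bias disappears.
- **Not every effect flatters feasibility.** A reader might infer that all the errors point one way, but the saliva step lowers recorded consent.
- **Refusals are not understated.** They are recorded directly, and an absent woman has not refused. Compliance among women actually asked is also a legitimate measure. The difficulty is only that no denominator is fixed and absent women have no category.
- **A missed visit is not a loss.** The Intervention section describes a miss after which the woman can still earn at her next session. It shows that non-attendance is distinct from withdrawal, not that silent drop-out will be common. Calling a woman lost solely because she missed the last session would go too far.
- **Baseline saliva is informative.** It is taken after consent, so a woman can refuse it. It should be shown separately, not discarded.
- **Part of this can be repaired later.** Attendance can be rebuilt from the surveys and saliva tests planned at every session. Women who decline at the nurse may not be recoverable if no one logs them.

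**Conclusion.** The concern holds in three parts of unequal strength.

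1. Loss to follow-up, taken from withdrawals alone, is biased low. The direction follows from the text. The size (20% read as 15%, 10% or 5%) rests on assumed shares.
2. Consent is probably overstated (60% read as 67% or 75% under assumed shares), on the natural reading that the assistant logs the women the assistant sees. The saliva step offsets this slightly, to about 57% to 59% if it acted alone with 5% to 10% of consenters testing negative.
3. Compliance with due samples is overstated only if absent women are left out. Hair is the most exposed, because it is collected once, at the end.

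The 20% and 60% are the plan's own planning values, used here as if true. The documents do not support a firm numerical bias for any of the three rates. They do support correcting the definitions, and starting the nurse-stage tally before recruitment, because decliners who are not logged then may be lost to the record.

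**What to change.** (a) **Consent.** At the existing nurse interview, tally every first-visit self-reported smoker who meets the other entry criteria, and use that tally as the denominator. Show the stage at which each woman did not enter (nurse, research assistant, written consent), with saliva-negative women as a separate step after consent.

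(b) **Loss to follow-up.** Define it to include women who permanently stop attending as well as those who withdraw, and report attendance at each session due.

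(c) **Compliance.** Report samples obtained over samples due. Show refusals separately from missed visits, and baseline saliva separately from follow-up. Give hair its own line.

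The cost is a small tally burden at an interview that already asks about smoking, and reworded outcome definitions. The design and sample size do not change. The reported rates will probably look less favourable.
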